## Abstract

**Background:**

The critical shoulder angle (CSA), which helps to predict patients who are at risk of rotator cuff tears (RCTs) with large degree and who are susceptible to osteoarthritis with low angle, has been identified as one of the most vital acromial parameters; anterolateral and lateral acromioplasties have been proven to be valid ways to reduce CSA. However, no study has compared the effect of different acromioplasties on the reduction of the large CSA (≥33°) clinically. Additionally, either anterolateral or lateral acromioplasty could not precisely correct large CSAs to a favorable range (30–33°) in each patient. Thus, we will propose a novel precise acromioplasty technique for the purpose of reducing CSA accurately and effectively, and compare the effectiveness of different acromioplasties on the reduction of the CSA.

**Methods:**

A total of 60 RCT patients who have indications for arthroscopic rotator cuff repair and with pre-operative CSA ≥33° will be recruited in outpatient center of Sun Yat-sen Memorial Hospital. Eligible participants will be randomly allocated to Group A (anterolateral acromioplasty), Group B (lateral acromioplasty) or Group C (precise acromioplasty) via a random, computer-generated number system. Three surgical plans will be made for each participant respectively by one professional surgeon according to the results of randomization allocation. The post-operative CSA will be measured 2 days post-operation. Follow-up will be maintained at 3, 6, and 12 months after surgery including the visual analog scale score, the University of California at Los Angeles score, the Constant Shoulder Score and the American Shoulder and Elbow Surgeon Shoulder Assessment Form. Finally, all outcomes will be assessed by two researchers who are blinded to the recruitment and allocation.

**Discussion:**

This is the first clinical trial to evaluate the impact of different acromioplasties on the reduction of the CSA. Additionally, this study will provide a new precise acromioplasty technique, which is a novel precision and individualized treatment to prevent degenerative RCTs by reducing the CSA.

**Trial registration:**

ChiCTR2000032343. Registered on April 26th, 2020.

## Background

Rotator cuff tears (RCTs) is a common shoulder disease in the general adult population [1, 2]. While the pathogenesis of degenerative RCTs are multi-faceted, the precise mechanisms are still not fully understood [3–5]. The acromial morphology has been identified as one of the important etiologic factors of degenerative RCTs [6–8]. Numerous studies have revealed that a type III acromion, higher acromion index, lower lateral acromion angles, and larger critical shoulder angles (CSAs) are significantly associated with degenerative RCTs [9–11].

The CSA, defined as the angle between the plane of the glenoid fossa and a line connecting the inferolateral point of the acromion with the inferior glenoid margin on standardized anterior radiographs [12], has been identified as one of the most accurate and vital anatomic predictors of the development of degenerative RCTs [13]. Several studies have documented that a CSA of more than 35° predicts RCTs, whereas a CSA of 30° or less is associated with glenohumeral osteoarthrtitis (OA) or superior labrum from anterior to posterior lesion (SLAP) [14–19]. Gerber et al. concluded that correcting a large CSA to 33° or less during arthroscopic rotator cuff repair (RCR) could help patients to achieve superior strength of abduction after the RCTs heal [20]. Similarly, we previously found that a reduction of a large CSA (≥33°) to a desired range (30–33°) may prevent RCTs and OA [21].

Arthroscopic anterolateral or lateral acromioplasty has been proven to change the pathologically increased CSA in cadaveric study [22, 23]. Some authors also reported that the CSA can be reduced significantly by anterolateral or lateral acromioplasty in vivo [20, 24, 25]. Furthermore, Kaiser et al. demonstrated that lateral acromioplasty decreased the CSA more significantly than anterolateral acromioplasty in a three-dimensional analysis [26]. Nevertheless, to our knowledge, no study has yet compared the effect of different arthroscopic acromioplasties on the reduction of the large CSA (≥33°) clinically. Besides, although these techniques can greatly reduce CSA, none precisely reduce large CSAs to the favorable range.

The primary goal of the current study is to propose the precise acromioplasty, which is a novel technique for the purpose of reducing the CSA sufficiently and accurately. The second goal is to conduct a prospective randomized clinical trial that will evaluate the effectiveness of different acromioplasties on the reduction of CSA.

## Methods

### Study design

This study is a prospective, single-center, parallel-design randomized controlled trial. This protocol has been developed according to the SPIRIT statement [27]. The trial has been prospectively registered in the Chinese Clinical Trial Registry (ChiCTR2000032343). The outline of the study was given in Fig. 1.

**Fig. 1 Fig1:**
[figure not shown]
Study flow diagram

### Recruitment and informed consent

This study will be conducted in Sun Yat-sen Memorial Hospital. Patients with rotator cuff tears (RCTs) who need arthroscopic rotator cuff repair (RCR) will be recruited from the outpatient center of Sun Yat-sen Memorial Hospital. After accomplishing baseline assessment and confirming the eligibility of the patients, the researcher will introduce the study purposes, procedures, possible risks etc. for approximately 45 min, and answer all the questions raised by patients and their families. Informed consent forms will be signed by each patient. After enrollment, participants will be coded with a unique number.

### Eligibility and exclusion criteria

The inclusion criteria are as follows: diagnosis of unilateral degenerative RCTs; pre-operative critical shoulder angle (CSA) ≥33°; required to receive arthroscopic RCR; willing to take part in this study; pre-operative three-dimensional computed tomography (3D-CT) and post-operative standard radiographs of shoulder were performed in our institution. The exclusion criteria are: history of shoulder trauma, and concomitant fracture or dislocation of shoulder; previous surgery of the involved shoulder; diagnosis of massive rotator cuff tears; concomitant frozen shoulder, glenohumeral osteoarthrtitis (OA) or other inflammatory arthritis; unable to give informed consent.

### Randomization

After informed consent, eligible participants will receive a unique number. Then, patients will be randomly allocated to either the anterolateral acromioplasty group (Group A), the lateral acromioplasty group (Group B), or precise acromioplasty group (Group C) via a random, computer-generated number system. The treating surgeon will determine surgical plans according to the results of the randomization allocation. Allocation will be based on a 1:1:1 ratio between the three different groups.

### Blinding

In this study, participants will be clearly informed of surgical plans before operation. Besides, the surgeon and assistant will perform acromioplasty along with arthroscopic RCR. Consequently, the patients, treating surgeon and assistant are not blinded to the group allocation. However, the surgeon and assistant will not participate in the pre-operative and post-operative assessment, and other researchers will blinded to the surgical decision making.

### Interventions

All patients will receive a routine examination during admission, including routine blood and urine tests, as well as evaluation of general condition. Imaging examination, such as a 3D-CT of shoulder and MRI (if necessary), will be completed before enrollment. All participants will complete standard anteroposterior radiography of shoulders 2 days post-operation and follow-up will be continued at 3, 6 and 12 months after surgery. This trial will involve three types of acromioplasty: anterolateral, lateral or precise acromioplasty. One of these acromioplasties will be randomly performed along with arthroscopic RCR in each group.

### Surgical procedures

One professional surgeon will make the surgical plan and conduct the arthroscopy in Sun Yat-sen Memorial Hospital. All participants will undergo general anaesthesia and be fixed in lateral decubitus. The surgery will begin with the establishment of a standard posterior portal and diagnostic arthroscopy. Then the arthroscopic RCR will be performed depending on the tear location and size. Later, three different acromioplasties will be conducted in groups A, B and C respectively according to a random allocation as previously described. The main processes of the acromioplasties are described below.

In group A, after the undersurface of the acromioclavicular joint and the anterolateral margin of the acromion are freed from all soft tissue via a 5 mm shaver burr (Arthrex Inc., Naples, USA), the surgeon will gradually resect the anterolateral acromion from the anterolateral corner, perpendicular to the line from the anterior third lateral edge of the acromion to anterior acromioclavicular joint line margin. The anterolateral acromioplasty in group A will involve a width of approximately 10 mm (two shaver burr widths).

In group B, after the undersurface and lateral margin of the acromion are freed from all soft tissue, the lateral acromioplasty will be started inferiorly at the middle lateral edge of the acromion, perpendicular to the line from the anterolateral to the posterolateral corner of the acromion. The lateral acromioplasty in group B will involve a width of approximately 10 mm (two shaver burr widths).

In group C, the pre-operative CSA (≥33°) will be measured on the 3D model. We will set 30° for the CSA as the post-operative target degree. Second, the virtual acromioplasty will be simulated and the resected bone border will be measured upon the Mimics (Materialise, Leuven, Belgium), including the anterolateral corner of acromion (A), anteromedial resection margin (B), posterolateral resection margin (C), and the distance of AB and AC. Third, the surgeon will identify and mark points A, B and C on the patient’s skin by measurement the distance of AB and AC according to the pre-operative planning above. Then, after the undersurface of the acromion are freed from all soft tissue, the surgeon will insert points A, B and C with spinal needles perpendicularly from the skin to the subacromial space as line marks, a resection line will be made from B to C during arthroscopy. Lastly, the region of the acromion outside the resection line will be gradually resected by a 5 mm shaver burr (Arthrex Inc., Naples, FL, USA) during arthroscopy. The main procedure is shown schematically in Fig. 2.

### Outcome measures

General information and baseline assessment will be collected during admission. The post-operative CSA will be measured 2 days post-operation. Follow-up will be maintained at 3, 6, and 12 months after surgery, including the visual analog scale (VAS) score, the University of California at Los Angeles (UCLA) score, the Constant Shoulder Score (CSS) and the American Shoulder and Elbow Surgeon (ASES) Shoulder Assessment Form. All outcomes will be assessed by two researchers who are blinded to the recruitment and allocation.

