### Data management

Participants will be coded with a study number after informed consent, and all data referring to patients will be documented by this number, not by name. A case report form (CRF) will be used for participants to collect information including baseline information, radiographic outcomes, and follow-up. Data will be collected at baseline admission and 2 days post-operation, as well as 3, 6 and 12 months post-surgery. Data on adverse events and further medical treatments will also be collected. The recording of data is assigned to a data manager who is accountable for it, and other researchers will be restricted from accessing study data.

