### Statistical analysis

The analysis of covariance will be conducted to compare the alteration of the CSA and shoulder function scores between randomized groups. The accuracy rates of different acromioplasties will be calculated, and χ^2^ test will be performed to evaluate the statistical differences between groups. The Spearman correlation coefficients will be used to assess the relationship between CSA and shoulder function scores. The intraclass correlation coefficient will be calculated to assess the consistency between researchers and between measurements of a single researcher. Statistical significance will be set at *P* < 0.05. All analyses will be carried out using SPSS 19 (IBM Corp, USA) by two researchers blinded to the recruitment and collection.

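### The two researchers who read each day-2 CSA also score function and are not masked to the angle, which can bias the secondary CSA–function correlation

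*Protocol article*

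**What the plan says.** In the protocol article, Outcome measures sets the order of events. "The post-operative CSA will be measured 2 days post-operation", and then "Follow-up will be maintained at 3, 6, and 12 months after surgery, including the visual analog scale (VAS) score", together with the UCLA, CSS and ASES. The section closes with "All outcomes will be assessed by two researchers who are blinded to the recruitment and allocation".

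Statistical analysis plans the association: "The Spearman correlation coefficients will be used to assess the relationship between CSA and shoulder function scores". It also plans a reliability analysis: "The intraclass correlation coefficient will be calculated to assess the consistency between researchers and between measurements of a single researcher".

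Three other places bear on the point:

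- Blinding says that, apart from the surgeon and assistant, "other researchers will blinded to the surgical decision making". This concerns the choice of operation, not the resulting angle.
- Data management says that "all data referring to patients will be documented by this number, not by name". It makes a data manager responsible for recording and restricts other researchers' access to study data.
- Shoulder function scores says that patients rank their own VAS pain. It does not say which UCLA, CSS or ASES items the assessor rates.

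Nowhere is a function assessor said to be masked to the CSA, and nowhere are film reading and function scoring given to different people.

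**The concern.** One pair of researchers produces one variable of the planned correlation and can influence the other. The angle is read at day 2 and function is scored months later, so any carry-over runs from film to score.

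The article also gives assessors a reason to expect a result. Background and Discussion present correction of a large CSA to 30–33° as desirable. The Discussion also cites studies in which reducing the CSA did not improve function, so the question is open. If assessors rate shoulders with a favourable angle a little higher, the correlation would partly reflect that expectation.

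Masking to allocation does not prevent this, because the angle is a different piece of information. The access restriction covers recorded data and cannot remove a value that the researcher measured.

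**Working it through.** **Step 1: what the text fixes.**

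| Element | Protocol article | Consequence |
|---|---|---|
| Who assesses | Two researchers, all outcomes | Same pair for CSA and function |
| Order | CSA at day 2; scores at 3, 6, 12 months | Angle read before function is scored |
| Masking | Recruitment, allocation, surgical decision | CSA not covered |
| Analysis | Spearman, CSA with function | Uses both sets of assessments |

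The planned agreement analysis, to "assess the consistency between researchers and between measurements of a single researcher", fits both members of the pair reading the CSA. It does not say that both read every film.

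**Step 2: numbers of patients.** The article gives 48 before dropout and 60 after: 48 / (1 − 0.20) = 60. A one-way ANOVA with means 2.6°, 4.4° and 4.8°, a common SD of 1.8° (the largest of the three stated) and alpha 0.05 gives 16 per group, that is 48, with power 0.9005. The stated sample size reproduces, and this point does not change it. The illustration uses 48 and 60.

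**Step 3: illustration of size.** The documents give neither the distribution of post-operative CSA nor any rating shift, so both are assumed. The article does not say which CSA enters the correlation; post-operative CSA is assumed.

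- CSA ~ Normal(mean, SD 2.5°), with no true relation to function.
- Score = Normal(0, 1) + shift × I(angle is favoured), with shifts of 0.2, 0.3, 0.4 and 0.5 SD.
- Result: share of simulated trials with Spearman P < 0.05. The nominal value is 5%.

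| Favoured angles | Mean CSA | n | 0.2 SD | 0.3 SD | 0.4 SD | 0.5 SD |
|---|---|---|---|---|---|---|
| all ≤33° | 31.5° | 60 | 7.9% | 11.6% | 17.1% | 24.3% |
| all ≤33° | 31.5° | 48 | 7.3% | 10.3% | 14.7% | 19.9% |
| 30–33° only | 31.5° | 60 | 4.7% | 5.1% | 5.2% | 5.3% |

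With only 30–33° favoured and n = 60, moving the mean changes the range over the same shifts: 5.4–6.8% at 32°, 6.3–11.1% at 32.5° and 6.8–15.4% at 33°. At 33.5° the rate is about 10% for 0.3 SD and 18% for 0.5 SD. Over n = 48–60 and all four shifts, the range at 33.5° is about 6–18%.

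**Step 4: why the form matters.** With mean 31.5°, the share below 30° is Φ((30 − 31.5)/2.5) = Φ(−0.6) ≈ 27%, and by symmetry the share above 33° is the same. A bonus for the middle band alone lifts neither end relative to the other. The relation is not monotone, and Spearman's test does not detect it. Once the mean moves up, more patients lie above the band than below it, and a monotone component appears.

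A shift linear in the angle gives more: about 11% for 0.1 SD of score per SD of CSA (n = 48 or 60), and 23% (n = 48) to 30% (n = 60) for 0.2. That form needs the assessor to recall the angle by degree, so it is not carried into the conclusion.

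**The case against.** The case against is substantial, and most of it limits the point without removing it.

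- **Recall.** The assessor would have to remember one numbered film among 60 patients at 3, 6 and 12 months, without access to stored readings. This stands: a reader might infer that the assessor necessarily knows each patient's angle, and the documents do not show that. They show only that nothing prevents it.
- **Film revealing the technique.** A reader might also infer that the operated acromion on the film discloses the arm. Nothing in the article supports this. Groups A and B are both resected to about 10 mm, and the assessors are stated to be masked to allocation.
- **Route of the bias.** Assessor rating cannot alter the VAS, which patients rank. For the other scores, a shift of 0.2–0.5 SD in the total would have to come through items that the article does not identify.
- **Importance.** The correlation is not one of the two goals in the Background, which are to propose the technique and to compare CSA reduction. Masking to allocation is what protects the randomised comparisons, and it is in place.
- **Condensation.** Film coding and reading order are details that an article may leave to a fuller document. That is fair for the details. But the article itself states who assesses and what they are masked to, and as stated the masking omits the CSA.

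**Conclusion.** The point holds as a modest one. The stated arrangement lets the CSA reading influence assessor-rated function items, and this can bias the secondary Spearman correlation. The VAS, the primary CSA comparison, the accuracy rate and the sample size are not affected.

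The size cannot be derived from the documents. Under the assumed shifts the false-positive rate runs from no inflation (about 5%) to about 24%, depending on which angles the assessor favours and where the post-operative CSA centres. The upper figure requires every angle of 33° or less to be favoured. That sits poorly with the article's own view that angles below 30° are linked to osteoarthritis. The figures illustrate the mechanism and do not predict the bias in this trial. The change is worth making because it is cheap, not because the bias is shown to be large.

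**What to change.** In Outcome measures, specify that the existing data manager:

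1. removes identifying information from the day-2 films;
2. gives each film a random reading code separate from the study number;
3. presents the films to the same two researchers under that code, in random order;
4. withholds the CSA values from those researchers until the last 12-month visit.

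In Blinding and in Outcome measures, state that function assessors are masked to post-operative CSA as well as to allocation.

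The cost is one code list and later availability of CSA readings to the study team. No extra staff, films, visits or patients are needed, and the planned agreement analysis is kept. The coding has to be in place before the films are read, because a film already read under the study number cannot be masked afterwards.

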### Primary outcome

#### Pre-operative CSA on 3D scapula

The pre-operative CSA of patients will be measured on 3D-CT model before enrollment. First, Digital Imaging and Communications in Medicine (DICOM) data from CT scans of the shoulders will be used to reconstruct 3D scapulae by Mimics (Materialise, Leuven, Belgium). Then, the 3D model will be imported into Blender (Amsterdam, Netherlands) and aligned to the local coordinate system according to the same criteria as described by Suter et al. [28]. Lastly, the CSA, which is measured as the angle between a line connecting the inferior border of the glenoid with the most inferolateral point of the acromion and another connecting inferior and superior glenoid margin [12], will be measured on anterior view using Blender (Fig. 3a). Patients with a native CSA ≥33° will be recruited as candidates.

**Fig. 3 Fig3:**
[figure not shown]
The measurement of the critical shoulder angle (CSA) on 3D scapula (**a**) and X-ray (**b**)

#### Post-operative CSA on X-ray

The post-operative CSA of participants will be measured on standard anteroposterior radiography of the shoulder (Fig. 3b). The efficacy is reflected in the reduction of CSA after acromioplasty. The accuracy is defined as the percentage of patients whose post-operative CSA decreased from a large angle (≥33°) to a normal range (30–33°) via acromioplasty.

### Secondary outcome

#### Shoulder function scores

Subjective pain will be ranked by the patients on the visual analog scale (VAS) score for pain, with 0 indicating no pain at all and 10 indicating the most severe pain the patient could imagine. The University of California at Los Angeles (UCLA) score, the Constant Shoulder Score (CSS) and the American Shoulder and Elbow Surgeon (ASES) Shoulder Assessment Form will be used for the functional assessment.

### Adverse event management

In this study, the different interventions for participants who are willing to receive arthroscopic RCR are three diverse acromioplasties, which are relatively safe procedures during minimally invasive surgery. Adverse events are defined as any unexpected medical incidents which happen in participants and do not necessarily have a causality with the acromioplasty, including acromial fractures, detachment of deltoid origin, and either pain or swelling due to bone removal of acromion. Participants will report any adverse events to doctors or study researchers as soon as they can. All adverse events will be documented and further medical treatment will be arranged if necessary. In addition, the participants will be closely followed up until conditions are resolved or their condition is stabilized.

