Although lateral acromioplasty has been documented to be the most effective way to decrease CSAs in vitro [22, 26], the post-operative angle is uncontrollable due to the insufficient or over-resection of the acromion. In other words, this is not always correct the large CSAs into the desired range of 30–33°. Additionally, lateral acromioplasty up to 10 mm has been considered a safe technique [20, 22, 42], yet some authors reported that over-resection of the acromion has potential complications, such as detachment of the deltoid origin and acromial fractures [43–45]. In 2017, Karns et al. introduced the concept of the critical acromion point (CAP), which is the most inferolateral part of the acromion and the key point used to determine the degree of the CSA on true anteroposterior radiograph. They also proposed a virtual acromioplasty on three-dimensional (3D) scapulae models with resection of the acromion parallel to the glenoid face of 2.5/5 mm medial to the CAP [46]. This technique seemed to have the equivalent effect in altering the CSA while preserving more bone volume when compared with lateral acromioplasty. However, only 80% of specimens with a native CSA of 38° or greater could be decreased to the acceptable range by this virtual acromioplasty; in addition, this technique has not been clinically realized so far.

To addresses the aforementioned deficiencies, we developed a precise acromioplasty technique, which is an individualized therapeutic strategy oriented by pre-operative virtual acromioplasty on 3D-CT model and software analysis, for the purpose of reducing the CSA with greater efficacy and accuracy. Theoretically, we can clinically decrease large CSAs to any desired specific angle by this technique without cutting acromion not contributing to the CSA. Additionally, we will conduct a prospective randomized clinical trial to examine patients with RCTs and a CSA of 33° or greater who undergo acromioplasty during arthroscopic RCR to evaluate the impact of different acromioplasties. This study will provide a new precision and individualized treatment to reduce CSA.

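### The adverse-event definition turns on expectedness and, for pain and swelling, on cause, so complication counts may be incomplete or inconsistently classified

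*Protocol article*

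**What the plan says.** The definition is one sentence in Methods, Adverse event management. It opens "Adverse events are defined as any unexpected medical incidents which happen in participants and do not necessarily have a causality with the acromioplasty" and continues "including acromial fractures, detachment of deltoid origin, and either pain or swelling due to bone removal of acromion". On capture, the section says "Participants will report any adverse events to doctors or study researchers as soon as they can", and then "All adverse events will be documented and further medical treatment will be arranged if necessary". The Data management section adds "Data on adverse events and further medical treatments will also be collected", next to a CRF and data collection at baseline, day 2 and months 3, 6 and 12.

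Two other places bear on this. The Discussion notes reports that "over-resection of the acromion has potential complications, such as detachment of the deltoid origin and acromial fractures". The Blinding section says "participants will be clearly informed of surgical plans before operation", and that patients, surgeon and assistant are unblinded. It keeps the surgeon and assistant out of assessment, and the Outcome measures section assigns all outcomes to two blinded researchers.

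**The concern.** A case definition for harms should let any two people classify the same event in the same way. This one uses two criteria that pull against the rest of the sentence. Expectedness is a condition of entry, yet the examples are events that the authors foresee. Cause is declared irrelevant, yet pain and swelling are described by their cause. The only route of capture that is spelled out is a report by the patient, who knows the allocation.

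The trial introduces a new, individually planned bone resection, and the same section describes all three procedures as relatively safe. At stake is whether the complication counts by group can be read as a fair description of what happened. The efficacy analysis and the sample size are not affected.

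**Working it through.** The plan states no adverse-event rate, count or target, so there is no figure to reproduce. The check is mainly a reading of the text, followed by a note on scale.

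**1. Expectedness.**
- The general clause in Adverse event management admits *unexpected* incidents.
- The examples are acromial fracture, deltoid detachment, and pain or swelling. The Discussion gives the first two as already reported complications of over-resection, so they are not unexpected to these authors. It does not mention pain or swelling.
- The word *including* brings the named items in despite the general clause. It does nothing for foreseeable events that are not named. Re-tear is an example: the Discussion cites studies linking a large CSA to re-tear after repair, and every participant has a CSA of 33° or more. Re-tear is foreseeable and unlisted, so on a literal reading it falls outside the definition.
- The promise to document all adverse events cannot repair this, because it reaches only what the definition admits.

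**2. Cause.**
- The general clause says that a causal link to the acromioplasty is not required.
- The example reads "either pain or swelling due to bone removal of acromion", which is a causal attribution.
- Under Interventions and Surgical procedures, every patient has the acromioplasty together with an arthroscopic cuff repair. Post-operative pain or swelling cannot readily be assigned to one of the two. One person may record a swollen shoulder under the general clause, and another may leave it out because it was not attributed to the bone resection.

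**3. Capture.**
- Adverse event management names one route, report by participants, to doctors or study researchers.
- Blinding says that those participants know their technique.
- Data management says that adverse-event data are collected, but not how events are elicited. The blinded assessors are assigned the outcomes; the article does not assign them adverse events.

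**4. Scale.**
- Inputs from Sample size calculation: 60 recruited, 60/3 = 20 per group; 48 evaluable, 48/3 = 16 per group.
- One event classified differently changes a group's observed rate by 1/20 = 5 percentage points, or 1/16 = 6.25 points.
- Assumed true rates, since the documents give none: at 5%, 10% and 20% the expected counts in 20 patients are 20 × 0.05 = 1, 20 × 0.10 = 2 and 20 × 0.20 = 4. One classification decision is a large share of such counts.
- Zero events in n patients excludes, at one-sided 95%, only true rates above 1 − 0.05^(1/n): 13.9% for n = 20 and about 17% for n = 16. This assumes complete capture. It follows from the sample size and would be the same after any rewording, so it does not measure the defect. It shows only that the counts carry little information.

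**The case against.** The strongest case on the other side is that the sentence works if read whole. The known complications are listed by name, documentation of all adverse events is promised, and *unexpected* is probably loose English for untoward. This is a single-centre trial with one surgeon, so sites cannot diverge. Pain is scored on the VAS at follow-up, a radiograph is taken on day 2, and the unblinded surgeon and assistant do not assess. A journal article may also leave a complication checklist to the full protocol or CRF.

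Much of this stands, and it rules out four stronger readings that a reader might infer:
- *The definition excludes the known complications.* It does not; they are expressly included.
- *Pain and swelling count only if due to bone resection.* The list illustrates a general clause, and the text does not contain that *only*.
- *Events are counted only if patients volunteer them.* Participant report is the only route stated, but it is not said to be the sole one. The follow-up content is introduced as including the scores, which is not exhaustive.
- *Counts will be too low and biased between techniques.* No complication rate or capture rate is given. All three groups are active acromioplasties under one reporting rule. Adverse events are not a listed outcome, and Statistical analysis plans no comparison of them.

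The wording itself is not answered. The likely intent of *unexpected* is not what the text says, and unlisted foreseeable events stay outside it. The VAS is an efficacy score; it does not cover swelling and is not an adverse-event record. The missing checklist alone would be no finding. It matters only because the route that is stated runs through unblinded patients.

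**Conclusion.** The point holds as a low-severity defect of definition. The sentence conditions adverse events on being unexpected while listing foreseeable ones, and disclaims causality while attributing pain and swelling to the bone resection. With participant report as the only stated route, counts may be incomplete or inconsistently classified. The documents do not support a claim that undercounting is certain or that it differs between techniques, and any figure for it would rest wholly on an assumed capture rate. The scale given (5 percentage points per event in a group of 20) follows from the planned group size alone. The conclusion assumes that the full protocol or CRF does not already carry a broader definition or structured questioning; if it does, the article's wording should be aligned with it.

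**What to change.** In Adverse event management:
- Define an adverse event as any untoward medical occurrence after surgery, whether or not expected and whether or not thought related.
- Delete *unexpected* and the attribution of pain and swelling to bone resection. Keep the named complications as examples.
- Record expectedness and relatedness as separate CRF fields, so that neither decides whether an event is counted.
- At the existing day 2 and month 3, 6 and 12 contacts, have the already blinded assessors put the same fixed questions to every patient. Suggested items are acromial fracture, deltoid detachment or weakness, new pain or swelling, and re-operation. Keep spontaneous reporting between contacts.
- Report counts by randomised group.

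The cost is a wording change, one CRF page and a few minutes at contacts that already exist. Recorded event rates will be higher than under spontaneous reporting, and the report should say so. Sample size, visit schedule and treatment are unchanged.
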